#### **8.1.3 Statistical Methodology**

Binary outcomes will be presented as proportions and relative risks with 95% confidence intervals, p values being calculated from the chi-square test or Fisher's exact test if numbers are small, with appropriate methods used for the calculation of CIs when numbers are small.

Continuous outcomes will be analysed using methods based on the Normal distribution where possible either if data are Normal or can be suitably transformed. Results will be presented as differences in means with 95% confidence intervals and modelled using multiple regression with baseline values as covariates.

Adverse events will be reported by treatment group, aggregated and given as number of children, total number of events, and incidence rates per year with 95% confidence intervals

Prognostic baseline variables will be inspected for any imbalance between the groups that is judged to be clinically important. If any such imbalance is observed, these variables will be included as covariates in sensitivity analyses for all key outcomes (please see section 8.2 below).

All analyses will be 2-sided with 5% significance level.

The sections below will outline the analyses for the main paper of the trial and describe what material will be reported in each table.

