#### **1. TRIAL DESIGN:**

This is a randomized controlled trial of the early introduction of allergenic foods (and other foods) from three months of age in the general population with target accrual of 1302 participants. Mothers were recruited initially antenatally from two large antenatal units (Kingston and St Thomas' Hospitals) (antenatal recruitment ceased November 2009) and subsequently postnatally using invitations mailed to parents who are members of the Bounty Parenting Club.

All infants will be followed up until three years of age by which point the impact of the intervention on the primary outcome (food allergy) and secondary outcomes - asthma (including atopic wheeze), eczema, allergic rhinitis (including aero-allergen sensitization), combined food allergy prevalence (including food sensitization) and the prevalence of combined allergic disease will be known. As described in the EAT Protocol, Figure 5, Overall Study Design

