#### **3. TRIAL ARMS**

**3.1 Early introduction group:** Dietetic controlled introduction of allergenic foods from three months of age. A pureed fruit / vegetable or baby rice mixed with breast milk or water commenced first, followed by cow's milk based yoghurt. Subsequently egg, sesame, fish, and peanut introduced in a randomized order, with wheat introduced last. (For further details on ingestion timing and quantities for each food, see protocol).

**3.2 Standard introduction group:** Standard introduction following current UK Government infant feeding advice (exclusive breastfeeding until around 26 weeks of age) and avoid introducing foods that may cause allergies before six months of age (cow's milk, egg, wheat, peanuts, tree nuts, seeds, fish and shell fish).

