## **7.3 Safety outcomes**

### **7.3.1.1 Adverse events – gastrointestinal symptoms**

*For each of these, the number of events will be analysed together with any associated morbidities or treatment as appropriate*

1. Diarrhoea
2. Constipation
3. Possetting
4. Vomiting
5. Colic

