#### **7.3.3 Anthropometric outcomes**

1. Weight, absolute and SDS at 3, 12 months and three years
2. Length, absolute and SDS, at 3, 12 months and three years
3. BMI, absolute and SDS, at 3, 12 months and three years
4. Head circumference, absolute and SDS, at 3, 12 months and three years
5. Mid upper arm circumference at 3, 12 months and three years
6. Skin fold thickness, subscapular and triceps, at 3, 12 months and three years

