##### Assessing the 'dose' of potentially allergenic food received

The following algorithm defines a scoring system that quantifies dose in a relatively simple way and yet allows the detection of a dose-response, albeit outside of the original randomization. Hence for each participant regardless of group, their score will be defined as follows:

- Each week up to 6 months of age (26 weeks) that a participant ate a particular food at 75% or more would be scored 1 and lesser consumption would be a zero
- Each food would therefore yield a total score of between 0 and a maximum of 13 (as max weeks=13)
- The scores will be summed over all foods to give a total food consumption score which will be categorized into quintiles
- The relationship between score quintiles and the primary outcome will be explored using logistic regression with a test for trend across the quintiles

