**TABLE 5: Safety outcomes and indicative outcomes as listed below by intervention group:**

1. Diarrhoea

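### Adverse events are summarised only in aggregate, with no age window, so the plan gives no separate comparison for the three-to-six-month period in which the arms' feeding instructions differ

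*SAP*

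**What the plan says.** The rule for adverse events is one sentence in SAP section 8.1.3: "Adverse events will be reported by treatment group, aggregated and given as number of children, total number of events, and incidence rates per year". Confidence intervals at the 95% level are to accompany the rates. The sentence does not say over what the events are aggregated (time, event type or repeat episodes), and it names no measure for comparing the arms. Section 7.3.1.1 adds that "the number of events will be analysed together with any associated morbidities or treatment as appropriate", again without a period.

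Table 5 in section 8.3.2, headed "Safety outcomes and indicative outcomes as listed below by intervention group", lists diarrhoea, LRTI, constipation, eczema, wheeze, URTI, bronchiolitis, other infections and hospital admissions without an age window. In the same table, weight has three time points, matching section 7.3.3: "Weight, absolute and SDS at 3, 12 months and three years".

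Three other places bear on timing:

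- **Trial arms (section 3).** The early group has "Dietetic controlled introduction of allergenic foods from three months of age", while the standard group is to "avoid introducing foods that may cause allergies before six months of age".
- **Dose score (section 8.1.2).** It counts weeks up to 26 weeks of age: "Each food would therefore yield a total score of between 0 and a maximum of 13 (as max weeks=13").
- **Trial design (section 1).** "All infants will be followed up until three years of age". Section 5 puts entry at three months of age.

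**The concern.** A natural safety question is whether giving allergenic foods to infants from three months of age causes gut, atopic or infective symptoms while they are being fed. The instructions to the two arms differ explicitly from three to six months, but no planned summary isolates that period.

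If events are counted from entry to three years, most of the person-time lies after the instructed difference has ended. A short-lived excess would then be averaged with a long stretch in which it may be absent, and a rate ratio close to 1 could be read as reassurance about the feeding period. If the period is simply left open, the window could be chosen after the data have been seen. Either way, the main safety table would not show directly what happened during early feeding.

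**Working it through.** **The plan's own figures.** The SAP gives no expected rate or power for adverse events, so there is no safety figure to reproduce. Its sample size does reproduce: 8% v 4%, two-sided 5%, 80% power and pooled variance without continuity correction give 553 per arm, and 553/0.85 rounds up to 651. The 553 is used below only as a number of children.

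**Inputs from the SAP**

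- Window in which the instructions differ: 3 to 6 months, 13 weeks = 0.25 year (section 3; dose score in 8.1.2).
- Follow-up: 3 months to 3 years = 2.75 years (sections 1 and 5).
- Children per arm after drop-out: 553 (section 4.0).

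**Assumptions (the SAP gives no values)**

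- Aggregation runs over the whole 2.75 years.
- The rate ratio is 2 within the window and 1 afterwards.
- The background rate after six months is λ = 0.5 or 1 episode per child-year. The rate within the window is m times that, with m = 1, 2 or 3.
- Counts are Poisson, with no overdispersion.

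**Step 1: share of person-time.** 0.25/2.75 = 1/11 = 9.1%.

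**Step 2: pooled rate ratio.** The formula is RR_pooled = (m × RR × 0.25 + 2.5)/(m × 0.25 + 2.5). With RR = 2:

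- m = 1: 3.0/2.75 = 1.09
- m = 2: 3.5/3.0 = 1.17
- m = 3: 4.0/3.25 = 1.23

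**Step 3: number of children affected.** P(at least one event) = 1 − exp(−expected events per child). With λ = 1 and m = 1:

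| Period | Standard arm | Early arm |
|---|---|---|
| 3–6 months | 1 − exp(−0.25) = 22.1% | 1 − exp(−0.50) = 39.3% |
| Entry to 3 years | 1 − exp(−2.75) = 93.6% | 1 − exp(−3.00) = 95.0% |

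A difference of 17.2 percentage points in the window becomes 1.4 points over the whole period.

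**Step 4: strength of signal.** z = ln(RR)/√(1/E0 + 1/E1), where E0 and E1 are the expected events in 553 children per arm. For λ = 1 and m = 1, the window has E0 = 138.25 and E1 = 276.5, so z = 6.65. The whole period has E0 = 1520.75 and E1 = 1659, so z = 2.45. All six cases:

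| λ after six months | m | z, window | z, whole period |
|---|---|---|---|
| 0.5 | 1 | 4.7 | 1.7 |
| 0.5 | 2 | 6.65 | 3.3 |
| 0.5 | 3 | 8.15 | 4.6 |
| 1 | 1 | 6.65 | 2.45 |
| 1 | 2 | 9.4 | 4.6 |
| 1 | 3 | 11.5 | 6.5 |

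The whole-period z is always well below the window z, but it falls below 1.96 in only one of the six cases. The expected excess in the total count is the same in both analyses (138.25 events for λ = 1, m = 1). Pooling does not remove those events; it sets them against a larger background.

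**The case against.** - **The period is not stated.** The SAP does not say that events are pooled to three years. The term for aggregation is undefined, and the sentence on follow-up in section 1 introduces the allergy outcomes, not adverse event collection. This stands: whole-period pooling is the natural reading, not the text. The unseen protocol may fix the collection period, but how events are summarised and tabulated belongs in the SAP, and section 8.1.3 states that rule without deferring to the protocol.
- **The end of the contrast is inferred.** A reader might infer that the arms differ in feeding only from three to six months. The SAP supports only that their instructions differ explicitly then; it does not give the standard arm's intake after six months. The dose score belongs to an explanatory analysis and does not define the randomised contrast. If intake differs for longer, the 1/11 dilution is too strong.
- **A real harm need not vanish.** A reader might infer that harm would be diluted to near nothing. In five of the six cases above the pooled z still exceeds 1.96, and event totals and rates do not saturate. Saturation affects one of three planned measures, and only for common events; it need not apply to hospital admissions.
- **The pooled rate is not biased.** A reader might infer bias toward no harm. A rate by randomised arm over full follow-up is a legitimate intention-to-treat estimate of net burden to age three. It can also show later or persistent effects, for example on eczema or wheeze, which a three-to-six-month comparison would miss. This stands, so the pooled rate should not be demoted.
- **Table 5 covers the main paper only.** A windowed table elsewhere is not excluded. That is true, but none is planned in the SAP.

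**Conclusion.** The point holds as a gap in specification that carries a loss of sensitivity. Followed as written, the SAP yields no adverse event comparison for the period in which the arms' instructions differ, and it leaves the aggregation period undefined.

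If the period is entry to three years, and if an effect is confined to three to six months, an assumed rate ratio of 2 is attenuated to between 1.09 and 1.23 over the background patterns examined, and the count of affected children says little for common events. These sizes rest on assumed rates and an assumed ratio. The documents do not support saying that the planned rate is biased or that any harm would be hidden. The primary endpoint is not affected.

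**What to change.** In section 8.1.3, define the adverse event observation period and say what is being aggregated. In 8.1.3 and Table 5, report each event by arm for enrolment to 6 months, over 6 to 12 months and over 12 to 36 months. For each window give the number of children, number of events, person-time, and the rate ratio with its 95% confidence interval. Pre-specify the enrolment-to-6-month comparison alongside the whole-period rate, so that one addresses harm during early feeding and the other net burden.

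This is a cheap improvement: SAP wording and a longer Table 5, with no new data provided events are dated. The downside is fewer events per window, and so wider intervals for rare events.

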#### **4.0 SAMPLE SIZE AND POWER**

The trial has 80% power to detect a 50% relative reduction in the absolute prevalence (from 8% in the standard introduction arm to 4% in the intervention arm) of food allergy by three years of age, assuming a 15%

drop out rate. These numbers were used to calculate the final cohort size of 1302 infants (651 infants in each arm) yielding a final cohort size of 1106 infants (553 infants in each arm) after drop out (based on the amended protocol September 2010). The whole cohort is to be followed up until the primary assessment point at three years of age.

The study is also designed so that it has sufficient power to detect a protective effect in the high risk sub-population. The high risk children are defined as being the 25% with eczema present at three months of age, who have an estimated prevalence of food allergy of 30%. It is estimated that with 15% loss to follow up, there will be 276 high risk children completing the study, 138 in each group. The study has 99% power to detect a reduction from 30% to 10% amongst the high risk participants in the intervention group and 85% to detect a reduction from 30% to 15%. See protocol (Protocol section 9.3: Contract variation September 2010). The study is not powered to detect a reduction in allergy to individual foods.

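### Adverse event rates get an interval for each arm but no between-arm estimate, unlike binary and continuous outcomes

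*SAP*

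**What the plan says.** SAP section 8.1.3 sets a reporting rule for each class of outcome.

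- Binary: "Binary outcomes will be presented as proportions and relative risks with 95% confidence intervals", with p values.
- Continuous: "Results will be presented as differences in means with 95% confidence intervals".
- Adverse events: by treatment group, "given as number of children, total number of events, and incidence rates per year with 95% confidence intervals".

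The same section adds that "All analyses will be 2-sided with 5% significance level".

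Section 7.3.1.1 says of the gastrointestinal symptoms that "the number of events will be analysed together with any associated morbidities or treatment as appropriate", without naming a method. The remaining adverse event and serious adverse event lists (7.3.1.2 to 7.3.2) name none either. Table 5, in section 8.3.2, is titled "Safety outcomes and indicative outcomes as listed below by intervention group". It lists nine event types (diarrhoea, LRTI, constipation, eczema, wheeze, URTI, bronchiolitis, other infections, hospital admissions) and two weight measures.

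**The concern.** The first two rules each end in a contrast between the arms. The adverse event rule ends in three descriptions of a single arm. Its confidence interval tells the reader how precisely the rate is known within one arm. It does not say by how much early introduction changes that rate, nor how large an excess is still compatible with the data.

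That excess is the safety question here. The intervention gives allergenic foods from three months of age to infants from the general population, and the comparison arm is advised to avoid them before six months. If the plan is followed as written, the main paper prints two intervals side by side and leaves the comparison to the reader. Checking whether the intervals overlap is a natural but poor way to make it.

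**Working it through.** **1. The plan's own figure.** The only power statement for the whole cohort concerns the primary outcome: "80% power to detect a 50% relative reduction in the absolute prevalence (from 8% in the standard introduction arm to 4% in the intervention arm"). With a two-sided 5% level, pooled variance and no continuity correction:

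n = [1.960 × √(2 × 0.06 × 0.94) + 0.842 × √(0.08 × 0.92 + 0.04 × 0.96)]² / 0.04² = 552.2, so 553 per arm.

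553 / 0.85 = 650.6, so 651 per arm and 1302 in all. Both agree with section 4.0. The SAP has no corresponding figure for adverse events.

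**2. What each rule delivers.**

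| Outcome class (8.1.3) | Per-arm figure | Between-arm figure |
|---|---|---|
| Binary | proportion | relative risk, 95% CI, p value |
| Continuous | – | difference in means, 95% CI |
| Adverse events | children, events, rate per year with 95% CI | none named |

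**3. What overlap would cost a reader who used it.** Let each arm's estimate have standard error s. The standard error of the difference is SE = s√2. Two 95% intervals separate only if the difference exceeds 2 × 1.96 × s = 1.96 × √2 × SE = 2.772 SE. A direct comparison needs 1.96 SE.

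- Effective two-sided level: 2 × [1 − Φ(2.772)] = 0.0056.
- An effect with 80% direct power lies at 1.960 + 0.842 = 2.802 SE. Chance of separation: Φ(2.802 − 2.772) = 0.512.
- An effect with 90% direct power lies at 1.960 + 1.282 = 3.242 SE. Chance of separation: Φ(3.242 − 2.772) = 0.681.

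These values hold for any two intervals with equal standard errors; they are not specific to this trial.

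**4. Scale in a trial of this size.** The SAP gives no event rates, so the standard-arm rates and rate ratios below are assumptions. Follow-up is taken as 553 children × 2.75 years (three months to three years) = 1,520.75 child-years per arm. Events are treated as Poisson, with intervals on the log scale.

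With E₀ and E₁ expected events, s₀ = 1/√E₀, s₁ = 1/√E₁ and SE = √(s₀² + s₁²):

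- direct power = Φ(log RR / SE − 1.96)
- chance of non-overlap = Φ([log RR − 1.96(s₀ + s₁)] / SE)

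Example: rate 0.05 per year, ratio 1.5. E₀ = 76, E₁ = 114, s₀ = 0.115, s₁ = 0.094, SE = 0.148 and log 1.5 = 0.405. Direct: 78%. Non-overlap: 49%.

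| Standard-arm rate per year | Ratio | Events, standard / early | Direct | Non-overlap |
|---|---|---|---|---|
| 0.02 | 1.5 | 30 / 46 | 41% | 15% |
| 0.02 | 2.0 | 30 / 61 | 88% | 65% |
| 0.05 | 1.5 | 76 / 114 | 78% | 49% |
| 0.10 | 1.25 | 152 / 190 | 54% | 24% |
| 0.10 | 1.5 | 152 / 228 | 97% | 87% |
| 0.50 | 1.25 | 760 / 950 | 99.6% | 97% |

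The Poisson assumption ignores repeat events clustering within a child. Clustering would widen the correct intervals and lower both power columns.

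**The case against.** The strongest reply is that the gap is narrower than it looks. Most of that reply stands.

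- **No overlap rule is planned.** A reader might infer that harms can be judged only by overlap. The SAP does not say so. The reported events and rate give child-time (events ÷ rate), so a crude rate ratio, and an approximate upper limit on the excess, could be worked out from the published table. That calculation would be post hoc, however, and aggregate totals cannot allow for several events in one child.
- **The binary rule may already cover part of this.** It is not restricted to efficacy, and section 8.3.2 places Table 5 among the secondary endpoints. Having at least one event is a binary outcome, so a relative risk can be read as already planned. Weight falls under the rule for differences in means. It would therefore be wrong to say that safety outcomes have no between-arm estimate at all. What remains is event counts and rates, which neither rule reaches.
- **Table 5's title proves nothing.** Similar by-group wording introduces the primary outcome and Table 4, where contrasts are intended. The point rests on the adverse event sentence in 8.1.3.
- **Descriptive reporting of adverse events is common.** That is so, and this is a weakness in reporting, not a wrong figure. But the SAP also speaks of analysing the number of events and applies a two-sided 5% level to all analyses. Both suggest a comparison, and no comparison of counts is defined.
- **The protocol may specify safety comparisons.** It was not available for this check. The SAP does, however, set its own rule for adverse events, and that rule stops at per-arm figures.

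**Conclusion.** The concern holds for adverse event counts and rates. The plan fixes a contrast for binary and continuous outcomes, but for event rates it fixes only per-arm figures with per-arm intervals. The safety table as specified will not show the excess or reduction in event rates with its uncertainty.

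The level of 0.0056 and the falls in power from 80% to 51% and from 90% to 68% apply only to a reader who judges by overlap, and assume equal standard errors. Under the assumed rates the loss ranges from about 29 percentage points (0.05 per year, ratio 1.5) or 30 (0.10 per year, ratio 1.25) down to about 3 (0.50 per year, ratio 1.25). It is material for uncommon events or modest ratios and small for very common events. The documents do not support a claim that the trial will miss particular harms, because they give no event rates.

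**What to change.** Amend the adverse event sentence in section 8.1.3, and Table 5 to match:

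1. For each adverse event type, report the incidence rate ratio, early v standard, with a 95% CI from a method that allows for repeat events in the same child. Examples are negative binomial regression with follow-up time as offset, or Poisson regression with robust standard errors by child. A plain Poisson interval would be too narrow if events cluster within children.
2. State that the binary rule (relative risk with 95% CI) applies to children with at least one event.
3. Keep the per-arm counts and rates as description, and base safety statements on the interval for the contrast, including its upper limit.

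The cost is one sentence and two columns, with no new data. The downside is more contrasts without multiplicity control: nine event types × two measures = 18 in Table 5. Present them as estimates with intervals, not as significance tests, and say that the general 5% sentence is not meant to turn them into tests.

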## **6. RANDOMIZATION AND BLINDING**

Participants are randomly assigned to treatment using a centrally administered randomization service (ALEA). The randomization is not stratified given the number of participants. Given the nature of the intervention, the study participants cannot be blinded to their allocation group. However, the study outcomes are based on food challenges that include double-blinded assessment and objective measures of sensitization (skin prick test results) and specific IgE measurements. The latter are measured by laboratory staff blinded to the child's allocation status.

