#### **8.2 Description of baseline data: TABLE 1**

Key variables collected at baseline will be summarised by treatment group. For continuous variables; means and standard deviations will be calculated and for categorical data, actual numbers and the calculated proportions will be shown. No formal testing of baseline characteristics between treatment groups will be performed in keeping with best practice.

1. Sex of infant
2. Birthweight
3. Gestational age
4. Number of siblings
5. Age of mother
6. Maternal education
7. Maternal and paternal asthma/allergy
8. Maternal/paternal smoking
9. Ethnic origin of mother and father
10. Pet ownership status
11. Mode of delivery
12. Allergenic food consumption during pregnancy
13. Allergenic food consumption during lactation pre enrolment
14. Infant eczema status at enrolment

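### The primary comparison is crude: eczema at enrolment, which carries most of the risk on the SAP's own figures, can enter only as an imbalance-triggered sensitivity analysis, so available precision is forgone

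*SAP*

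**What the plan says.** SAP 8.1.3 analyses binary outcomes by proportions and relative risks, with a chi-square p value, or Fisher's exact test when numbers are small. SAP 8.3.1 applies this to the primary endpoint and adds no covariate. Baseline variables are inspected for imbalance of clinical importance, and then: "If any such imbalance is observed, these variables will be included as covariates in sensitivity analyses for all key outcomes". No other route brings a baseline variable into a binary comparison.

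Three other places bear on this:
- SAP 4.0 singles out a high-risk group: "The high risk children are defined as being the 25% with eczema present at three months of age". It puts food allergy at 30% in that group and powers a comparison within it.
- SAP 8.2 lists "Infant eczema status at enrolment" as the last of 14 baseline variables, so the variable is in hand.
- SAP 6 states: "The randomization is not stratified given the number of participants".

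**The concern.** The SAP builds its high-risk subgroup on one baseline variable and then leaves that variable out of the main comparison. When a factor explains much of the outcome, analysing within its levels removes that variation from the standard error. The crude test does not use this gain.

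Because allocation is unstratified, the arms may also differ by chance in their share of infants with eczema. The headline relative risk and p value would carry that difference uncorrected, and the adjusted result would appear only as a sensitivity analysis. Observed imbalance is also a poor trigger for adjustment. The precision gain comes from prognostic strength and is there even when the arms are balanced.

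**Working it through.** **Inputs.** From SAP 4.0: 80% power; control and intervention risks of 8% and 4%; 553 analysed per arm after 15% drop-out from 651; 25% with eczema; 30% food allergy among them. From SAP 8.1.3: "All analyses will be 2-sided with 5% significance level".

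**Step 1: reproduce the plan.** Pooled risk is 0.06.
- Null variance term: 2 × 0.06 × 0.94 = 0.1128.
- Alternative variance term: 0.08 × 0.92 + 0.04 × 0.96 = 0.0736 + 0.0384 = 0.1120.
- n per arm = (1.96√0.1128 + 0.842√0.1120)² / 0.04² = 553 after rounding up; 553 / 0.85 = 651 per arm, 1302 in total.
- Power at 553 per arm is 80.1%.
- With 138 per arm, the high-risk powers are 98.8% (stated 99%) and 85.1% (stated 85%).

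The plan's figures are therefore right for the crude test.

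**Step 2: what the figures imply about eczema.** The eczema stratum contributes 0.25 × 30% = 7.5 of the 8 percentage points in the control arm (94%). The remaining infants have (8% − 7.5%) / 0.75 = 0.67%. The risk ratio is 30 / 0.67, about 45.

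**Step 3: power when stratified.** Assume risk is halved in each stratum: 30% to 15%, and 0.67% to 0.33%. The overall difference is still 4 points.
- Alternative variance term within strata: 0.25 × (0.2100 + 0.1275) + 0.75 × (0.00662 + 0.00332) = 0.0844 + 0.0075 = 0.0918. The ratio to the crude term is 0.0918 / 0.1120 = 0.82, an 18% reduction.
- Null variance term within strata: 2 × (0.25 × 0.225 × 0.775 + 0.75 × 0.005 × 0.995) = 0.0947.
- Power = Φ[(0.04 − 1.96√(0.0947/553)) / √(0.0918/553)] = Φ(1.11) = 86.7%.
- Simulation of 200,000 trials: 80.8% crude, 87.1% stratified. With no effect, rejection is 5.0% for both tests.
- With a continuity correction on both tests: 77.5% and 83.8%.
- If the whole effect lies in the eczema stratum (30% to 14%): 80.9% and 86.6%.
- About 461 analysed per arm would give 80% power under stratification, against 553 planned.

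**Step 4: dependence on the 30% figure.** Overall risk is held at 8%, the eczema share at 25%, and risk is halved in each stratum (simulated):

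| Risk with eczema | Implied risk without | Crude power | Stratified power | Gain (points) |
|---|---|---|---|---|
| 30% | 0.67% | 80.8% | 87.1% | 6.3 |
| 25% | 2.33% | 80.9% | 84.5% | 3.6 |
| 20% | 4.00% | 80.8% | 82.6% | 1.8 |
| 15% | 5.67% | 80.8% | 81.4% | 0.6 |

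**Step 5: chance imbalance.** The between-arm difference in eczema share has SD √(2 × 0.25 × 0.75 / 553) = 2.6 points. A gap above 3 points in either direction occurs in about 25% of trials. At 30% against 0.67%, a 3-point gap moves the control-level risk by 0.03 × 29.3 = 0.9 points. In simulated trials where the intervention arm has more than 3 points excess eczema, crude power is just under 60%, against 87% stratified. With no true effect, the crude test rejects in between 9% and 10% of those trials, against 5% stratified. The opposite imbalance flatters the intervention, and over all trials the crude test is correct at 5%.

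**The case against.** The strongest reply is that nothing here is an error. The crude relative risk with a chi-square test is prespecified, controls type I error and matches the sample size calculation. All of that stands. A reader might infer that the trial is 6 points short of its power. It is not: it delivers the 80% it states, and the 6 points are precision left unused.

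The size is also open to challenge. The 0.67% is a residual from rounded planning estimates, the SAP does not state it, and it reaches zero if the eczema-stratum risk is 32% (0.25 × 32% = 8%). Halving risk in both strata is an assumption of this check. So 6 points is the top of the range in Step 4. The SAP does not itself rank eczema against other predictors; its strength is inferred from the three planning figures.

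Two further inferences fail:
- One might say that the imbalance rule makes the primary result data-dependent. It does not, because the rule reaches only sensitivity analyses.
- One might also see an inconsistency with continuous outcomes, which are modelled with baseline values. Those are most naturally earlier measurements of the same quantity, and the primary outcome has none.

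Sparse data is a fair objection to a careless fix. Under the planning figures the stratum without eczema holds about 415 × 0.67% = 2.8 and 415 × 0.33% = 1.4 events in the two arms, and single foods would be sparser still. The Cochran-Mantel-Haenszel test copes with this for the composite primary endpoint, but the small-number methods must stay for the single foods.

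**Conclusion.** The point holds as a question of efficiency and of robustness to chance imbalance. It does not affect validity. The primary analysis forgoes precision available from a variable that the SAP itself uses to define high risk.

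On the SAP's figures, with risk halved in both strata, power rises from about 81% to about 87%. The gain is about 4, 2 and 1 points if the eczema-stratum risk is 25%, 20% and 15%. Type I error is about 5% throughout, and none of the scenarios tried showed a loss. The case for protecting the headline result against eczema imbalance also weakens as the stratum risks converge. The change should be made, but the planned analysis would remain interpretable without it.

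**What to change.** In SAP 8.1.3 and 8.3.1:
- Make the primary analysis the Mantel-Haenszel relative risk with 95% confidence interval and the Cochran-Mantel-Haenszel test, stratified by eczema at enrolment (yes/no).
- Report the crude relative risk and chi-square p value as supportive.
- Keep Fisher's exact test and the small-number confidence intervals for sparse outcomes such as the single foods.
- Let adjustment for the other baseline variables in 8.2 stay as a sensitivity analysis, but state that adjustment for eczema does not depend on an observed imbalance.

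The cost is SAP wording only. The variable is already collected, the relative-risk measure is kept, and the sample size does not change. The change should be fixed before outcomes are compared by arm.
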